#### Secondary Study Parameters- Clinical

Of the clinical secondary outcomes, response (≥35% reduction in Y-BOCS I) and remission (Y-BOCS I ≤12) will be investigated using generalized linear mixed models (LMM, mixed-effects logistic regression). Pre-to-post changes in Y-BOCS II, CGI score, QoL, depression, tics, and anxiety will be tested using LMM analysis for repeated measures. The model will include fixed effects for time, study center, and the group-by-time interaction, but not for the group indicator alone, in order to adjust for potential baseline differences in the outcome variable. The group-by-time interaction term represents the between-group intervention effect and therefore constitutes the primary parameter of interest. Tolerability and side effects will be reported as absolute numbers and described qualitatively.

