### Randomization

Participants are randomized in a 2:1 ratio to one of 2 treatment arms, with twice as many participants allocated to receive active stimulation of the pre-SMA compared to sham rTMS. This unequal allocation was chosen to maximize the number of participants receiving the active intervention and to enhance recruitment by increasing the probability of assignment to active treatment.

Randomization is stratified by study sites to ensure balanced allocation across centers. Randomization sequences are generated using Castor EDC. Each site implements block randomization using randomly permuted blocks of size 6 to maintain allocation balance within each center and minimize group size imbalances that may arise due to site-specific factors, such as varying levels of experience with rTMS.

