### Sample Size Calculations

Meta-analyses [41,42] suggest an average effect size of 0.71‐0.79 (Hedges’ g) for the effect of rTMS as monotherapy. Our own meta-analysis [8] showed a lower Hedges’ g of 0.50. We use rTMS in addition to intensive 4-week daily ERP, and we therefore conservatively lowered the expected effect size to 0.4, in line with, for example, the augmentative effect of antipsychotics to either SSRI or cognitive behavioral therapy [59]. The effect size 0.4 corresponds to a pre-post intervention decrease in Y-BOCS I score of 4 points, which we consider a minimal clinically important difference (MCID). Our design uses a 2:1 randomization across the 2 conditions, with twice as many participants in the verum rTMS group. Using a significance level of alpha=.05, a 2-tailed comparison between means, and an estimated power of 0.8, the study requires 150 participants in the verum-rTMS arm and 75 in the sham-rTMS arm. Assuming a 10% dropout rate, we will include (225/0.9=) 250 participants. Participants are considered dropouts if they complete less than 60% of the minimum required 20 rTMS+ERP sessions, corresponding to fewer than 12 sessions. We apply stratified block randomization, with study center as the stratification factor, to ensure balanced allocation of conditions across centers. Although we will take the stratified design into account when analyzing the data by using it as a covariate, we will ignore its effect on the required sample size [60].

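### The mixed model for the continuous secondary outcomes includes study center only as a main effect, so center differences in pre-to-post change are not fully adjusted for and, if present, make the tests slightly conservative

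*Protocol article*

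**What the plan says.** In the protocol article, Secondary Study Parameters - Clinical names the outcomes and the method: "Pre-to-post changes in Y-BOCS II, CGI score, QoL, depression, tics, and anxiety will be tested using LMM analysis for repeated measures". It then lists the fixed effects: "The model will include fixed effects for time, study center, and the group-by-time interaction, but not for the group indicator alone". The tested quantity is defined next: "The group-by-time interaction term represents the between-group intervention effect and therefore constitutes the primary parameter of interest". Center appears once, as a main effect, and no center-by-time term is listed. Response and remission are assigned to a separate mixed-effects logistic model whose center terms are not spelled out.

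On the design side, the Randomization section states "Randomization is stratified by study sites to ensure balanced allocation across centers", using blocks of 6 at 2:1 within site. Sample Size Calculations says "we will take the stratified design into account when analyzing the data by using it as a covariate".

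**The concern.** With no group main effect, the arms share one baseline mean, and the group-by-time term is the baseline-adjusted posttreatment difference between arms. To gain the precision that stratification by center offers, the analysis should remove center differences in posttreatment score given baseline. A single coefficient per center, applied equally before and after treatment, suits centers that recruit more or less severe cases. It does not suit centers that obtain more or less improvement.

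The article gives some reason to think improvement could vary. The Randomization section mentions site factors "minimize group size imbalances that may arise due to site-specific factors, such as varying levels of experience with rTMS", and the sites use two makes of stimulator. Any such variation left in the posttreatment residual inflates the estimated error of a contrast that the design has already protected from it. What is at stake is a modest loss of power on the continuous secondary outcomes.

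**Working it through.** **The plan's own figure.** The article gives no standard error or center variance for this model. Its sample size does reproduce. For 0.4 SD, two-sided 0.05 and 80% power at 2:1, the sham arm needs 1.5 × (1.960 + 0.842)² / 0.4² = 73.6, so 74, with 148 verum. With the noncentral t, 75 + 150 is the smallest 2:1 size that reaches 80% (80.4%). Then 225 / 0.9 = 250. The check below uses 225.

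**Assumptions not in the document.** Pre and post SDs of 5 and 7; correlation 0.45; five centers of 75, 45, 35, 35 and 35; an effect of 2.4 points; unstructured 2 × 2 residual covariance; no random center terms. Centers differ only after treatment, with between-center SD k.

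**Step 1: what the shared center coefficient picks up.**
- The covariance is 0.45 × 5 × 7 = 15.75.
- The weight on the baseline mean is (49 − 15.75) / (25 + 49 − 31.5) = 33.25 / 42.5 = 0.782, leaving 0.218 on the posttreatment mean.
- A posttreatment-only center shift b therefore enters the coefficient as 0.218b. The residual shifts are −0.218b at baseline and 0.782b after treatment.
- The slope of post on pre is 15.75 / 25 = 0.63. The shift left in the residual of post given pre is 0.782b + 0.63 × 0.218b = 0.919b.

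So about 8% of the shift is absorbed and 92% remains.

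**Step 2: standard error.**
- The residual variance of post given pre is 49 × (1 − 0.45²) = 39.08.
- Unequal centers spread the participants by the factor 1 − Σp² = 1 − 11,325 / 50,625 = 0.776.
- The approximate ratio of the standard error as written to that with center-by-time is √(1 + 0.776 × (0.919k)² / 39.08).

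| k (points) | Ratio by formula | Excess in simulation | Power as written | Power with center-by-time |
|---|---|---|---|---|
| 1 | 1.008 | 1.4% | 75.7% | 76.5% |
| 2 | 1.033 | 3.9% | 73.9% | 76.5% |
| 3 | 1.073 | 7.6% | 71.9% | 77.1% |

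The simulation used 225 participants, five uneven centers, 2:1 blocks of 6 and 1,500 runs per setting. Its excess includes about 0.7% that arises from degrees of freedom even when centers do not differ. A separate simulation gave about 1%, 4% and 7%. At k = 3, the type I error was 2.8% as written against 4.3% with the added term. With 250 participants and a larger leading center, power losses were 1.2, 2.9 and 5.6 points.

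**Step 3: sensitivity.**
- With equal SDs before and after, the shift left over falls to 0.5 + 0.45 × 0.5 = 0.725 of b, and the simulated excess to 1.0%, 2.4% and 4.7%.
- In standardized units over correlations 0.3 to 0.7, center variance in change of 5%, 10% and 20% of residual variance gave an excess of 1.6–3.9%, 2.6–6.9% and 4.5–12.3%.
- With stable center differences only (SD 0.3 at both times, correlation 0.5), the standard errors were 0.1225 as written, 0.1217 with center-by-time and 0.1232 with no center term. The as-written model removes these apart from the 0.7% artefact.
- The estimate showed no material bias in any setting.

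**The case against.** Several points on the other side stand.

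- **Stable differences are handled.** A reader might infer that the model does not adjust for center at all. That is not supported: differences equal at both times are removed, and posttreatment-only differences are partly absorbed. At 10% of residual variance and correlation 0.5, the excess is 3.9%, against 5.8% with no center term.
- **The excess is conditional.** A reader might infer that the standard errors are too wide as a fact. They are only if improvement differs between centers, and no such variance is given. The 3-point case is 9 / 39.08 = 23% of residual variance and exceeds the assumed 2.4-point effect, so it is an upper scenario.
- **There is no contradiction with the sample size section.** A center main effect is an ordinary reading of using the stratification factor as a covariate.
- **The evidence for site differences is thin.** The Randomization remark concerns group sizes, and the challenges section concerns start-up and recruitment. The article also describes operator training, a common ERP manual and several clinicians per patient.
- **The scope is limited.** A reader might extend the point to all secondary tests. The quoted model does not cover response and remission.

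The remaining objection is that a condensed article leaves model detail to the analysis plan. That would excuse an unstated covariance structure. It does not excuse this point, because the article writes out the list of fixed effects, and the list can be judged as written.

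**Conclusion.** The point holds in limited form and is minor. As listed, the fixed effects do not fully adjust the arm contrast for center differences in pre-to-post change. If there are such differences, the model standard error is too wide by about 1%, 4% and 7% for between-center SDs of 1, 2 and 3 points, with a power loss of roughly 1 to 6 points. Those sizes rest on the assumed SDs, correlation, center sizes and covariance structure, and they shrink if pre and post SDs are equal. The error is conservative, so it cannot produce a false claim for rTMS beyond the nominal rate. The primary ANCOVA is not at issue here.

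**What to change.** In Secondary Study Parameters - Clinical, and in the preregistered analysis plan, list the fixed effects as time, study center, center-by-time and group-by-time, still without a group main effect. The center terms then adjust the posttreatment contrast as a center covariate does in an ANCOVA, and the model fully reflects the stratified randomization.

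For two time points and five centers this adds four parameters and needs no new data. When centers did not differ, simulated power was 77.3% with the term and 76.8% without, so there is no measurable penalty. Posttreatment assessments are projected to finish in December 2026, which leaves time to make the change before unblinding.

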### Participants

We aim to include 250 adults with OCD (aged 18 y and older) who have not responded to at least 8 sessions of state-of-the-art ERP. The inclusion and exclusion criteria are designed to target individuals whose symptoms are insufficiently managed by standard treatments (ERP with or without serotonergic antidepressants) but who have not yet progressed to more invasive interventions such as DBS. Eligibility requires a primary diagnosis of OCD according to the *Diagnostic and Statistical Manual of Mental Disorders, Fifth Edition* (*DSM-5*) criteria, with symptom severity in the moderate to severe range as indicated by a Yale-Brown Obsessive Compulsive Scale (Y-BOCS)-I score of 16 or higher [34]. Exclusion criteria consist of recent changes in psychotropic medication (less than 8 wk before the trial), hoarding as the main symptom dimension, presence of a psychotic disorder, bipolar disorder, autism spectrum disorder (when this dominates the clinical profile, ie, is diagnosed as the primary disorder), substance use disorder, and current suicidal ideation with intent. Participants are also excluded if they are unable to safely undergo TMS treatment due to contraindications such as metallic implanted devices (eg, pacemakers and cochlear implants), epilepsy, any neurological disorder that causes a lesion to the brain and increased seizure risk (such as multiple sclerosis, previous serious head trauma, and stroke), pregnancy, chronic benzodiazepine use, or had rTMS in the past (for blinding reasons). Participants with severe claustrophobia who were unable to undergo MRI scanning were still eligible to participate in the trial.

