### Outcome Measures

Primary outcome and primary endpoint:

The primary outcome is the severity of OCD as measured by the Yale-Brown Obsessive-Compulsive Scale I (Y-BOCS-I) [34]. The primary endpoint is the difference between the active and sham intervention groups in posttreatment severity of OCD, estimated using an analysis of covariance (ANCOVA) model that adjusts for pretreatment severity of OCD. The intervention effect will also be reported as a standardized mean difference.

Secondary outcomes - clinical:

Response (=35% reduction on Y-BOCS I) [44].Remission (Y-BOCS I<12) [44].The severity of OCD, as measured using the newer version of the Yale-Brown Obsessive-Compulsive Scale - Y-BOCS II [37,45]. A combined version of the Y-BOCS I and II is administered pretreatment and posttreatment. Additionally, Y-BOCS-II severity scores are collected weekly during treatment and at all follow-up sessions, enabling comparison between the 2 versions and potentially supporting further implementation of the newer Y-BOCS II.The clinical global impression (CGI) severity scale [46].Comorbid depression symptoms, measured using the Beck Depression Inventory (BDI) at baseline, posttreatment, and follow-up [47]. In addition, we administer a VAS for depression at these same time points, plus every week during treatment, to monitor treatment response on mood. The simultaneous administration of VAS and BDI at baseline and posttreatment will allow us to scale and validate the VAS relative to the BDI, while offering a much quicker and simpler assessment for the participants.Anxiety, measured using the Beck Anxiety Inventory (BAI) and a VAS, following the same procedure and rationale as for depression [48].For participants with comorbid tics, as identified using the Yale Global Tic Severity Scale (YGTSS) [49], tic severity will be assessed using the same scale.Tolerability of the treatment and side effects, using an in-house questionnaire developed as part of our previous TIPICCO trial [19].

Secondary outcomes - cost-effectiveness

Societal costs will be measured using the iMTA Productivity Cost Questionnaire (iPCQ) [50] and the iMTA Medical Consumption Questionnaire (iMCQ) [51].QoL (EQ-5D-5L) [52]. Quality-adjusted life-years (QALYs) are the most important outcome measure for health care decision makers when deciding about the reimbursement of health care interventions.

Secondary outcomes - neuroplasticity:

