### Statistical Analyses

All statistical analyses for testing efficacy and cost-effectiveness will be done according to the intention-to-treat principle. Additionally, neuroplasticity will be analyzed based on the per-protocol sample, using a minimum number of 12 rTMS-ERP sessions as the threshold for adequate treatment. The significance level will be set at alpha=.05, 2-tailed. Safety data (eg, side effects and serious adverse events) are collected and summarized in the study results. A description of the analyses for the primary, secondary, and exploratory objectives is provided below.

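### The one stated secondary-outcome model adjusts through a baseline value that response and remission lack; whether it covers them, and at which visits they can be scored, is unclear

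*Protocol article*

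**What the plan says.** All of this is in the protocol article.

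- **Secondary Study Parameters- Clinical.** Response and remission "will be investigated using generalized linear mixed models (LMM, mixed-effects logistic regression"). The next sentence gives Y-BOCS II, CGI, quality of life, depression, tics and anxiety to a repeated-measures linear mixed model. One specification follows: fixed effects for time, study center and group-by-time, "but not for the group indicator alone, in order to adjust for potential baseline differences in the outcome variable". The interaction is named as the parameter of interest. No other fixed effects are listed for the logistic models, and the abbreviation LMM is attached to both model types.
- **Participants.** Entry requires a "Y-BOCS)-I score of 16 or higher".
- **Outcome Measures.** Response is a 35% reduction on Y-BOCS I. Remission is "Remission (Y-BOCS I<12"); the analysis section uses 12 or below. The combined Y-BOCS I and II is given before and after treatment; during treatment and at follow-up only Y-BOCS II is collected.
- **Table 1.** Y-BOCS I appears pre- and posttreatment only. Response and remission appear at posttreatment and FU1-FU3, with no pretreatment entry.
- **Primary Study Parameter.** The primary comparison is an ANCOVA adjusted for baseline Y-BOCS I.

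**The concern.** Leaving out the group term makes the arms share one baseline mean, and later differences are then judged against it. The device needs an outcome that is measured at baseline and varies there. Response and remission are not such outcomes, so the stated rationale fails for them.

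They are the first two clinical secondary outcomes listed, and the paragraph offers an analyst no other specification to use. Depending on how it is coded, it gives either a posttreatment odds ratio fixed at 1 or an estimate with no baseline adjustment. Remission is an absolute cut-off, so a chance difference in baseline severity would carry straight into that comparison. In addition, both outcomes are defined on a scale that is not scheduled at three of the four visits where Table 1 lists them.

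**Working it through.** **1. The plan's sample size, for context.** Inputs from Sample Size Calculations: effect 0.4, two-sided alpha 0.05, power 0.8, allocation 2:1. Normal approximation: sham n = (1 + 1/2) × (1.960 + 0.842)² / 0.4² = 1.5 × 7.85 / 0.16 = 73.6, so 74 + 148 = 222. The t-test version gives 74.2, so 75 + 150 = 225, and 225/0.9 = 250. The plan's figures reproduce. The point below concerns model structure and does not depend on them.

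**2. Baseline information.** At baseline, response is undefined or 0 for everyone. Remission (below 12, or 12 and below) is 0 for anyone still scoring 16 or more. The baseline indicator therefore has zero variance. The baseline measurement follows screening, so this assumes no one has dropped to the remission range in between.

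**3. What the stated terms do on the Table 1 visits.** Without a group term, the arm log odds ratio at visit t is the interaction δ_t.

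- Posttreatment as reference, interactions at FU1-FU3 only: δ_post = 0 by construction.
- Linear time starting at 0 at posttreatment: δ × 0 = 0.
- Categorical time with a contrast at every visit (what a standard formula parser builds from time plus time-by-group): δ_post is estimated, but baseline severity does not enter.

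A random-intercept logistic simulation shows the difference. It used 150 vs 75 participants, four visits and 60 runs. The 57.4% active response rate comes from Anticipated Findings; the sham rate of 40% and random-intercept SD of 2 are assumed. The true conditional log odds ratio was 1.16. With a contrast at every visit, the posttreatment estimate averaged 1.22. With reference coding it was 0, and the follow-up estimates shrank to 0.67-0.75.

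**4. Baseline added as a row of zeros** (ordinary logistic fit). Take 86/150 vs 30/75 responders. The crude log odds ratio is ln(86/64) − ln(30/45) = 0.296 + 0.405 = 0.70, with SE = √(1/86 + 1/64 + 1/30 + 1/45) = 0.29. The fitted group-by-time term is the same, 0.70 (SE 0.29). The baseline intercept diverges (−11.6, −26.6, −36.6 after 10, 25 and 50 iterations). The treatment contrast survives, but nothing is adjusted.

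**5. Visits at which the outcomes can be scored.** Y-BOCS I exists pre- and posttreatment; response and remission are defined on Y-BOCS I; hence they can be scored at posttreatment only. With a single visit, time does not vary, so there is no usable group-by-time effect, and the group term that would carry the comparison is the one left out.

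**6. Value of adjusting for baseline Y-BOCS I.** Change SD = 10.836/1.66 = 6.5 (Anticipated Findings, if that d was standardized by the change SD), so the arm difference is 0.4 × 6.5 = 2.6 points. Assumed: baseline mean 24-28, SD 4-5, truncated to 16-40; posttreatment SD 6.5; sham change −8.5. Each scenario has 150 vs 75 participants and 3000 trials. Efficiency is the squared ratio of mean z, adjusted over unadjusted.

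| Baseline mean | Correlation | Remission power, unadjusted | Adjusted | Efficiency |
|---|---|---|---|---|
| 24 | 0.5 | 0.616 | 0.677 | 1.16 |
| 26 | 0.5 | 0.542 | 0.607 | 1.15 |
| 28 | 0.5 | 0.460 | 0.514 | 1.13 |
| 26 | 0.3 | 0.554 | 0.571 | 1.05 |
| 26 | 0.6 | 0.553 | 0.665 | 1.25 |

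Repeating this with baseline SD 4.5 gave gains of 12-16% at correlation 0.5, 5% at 0.3 and 23% at 0.6. Response power moved by less than one point throughout.

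**The case against.** A reader might infer that the plan fits the no-group-term model to response and remission and so forces their posttreatment odds ratio to 1. The document does not support that. The specification directly follows the sentence on the repeated-measures model for continuous outcomes, all of which have a pretreatment visit, and its stated purpose fits only such outcomes. For them it is standard and valid. The zero also depends on coding, and a coding that removes the posttreatment effect would contradict the plan's own statement that the interaction carries the treatment effect. This objection stands against the strong reading. It leaves the ambiguity: the text does not limit the specification, and uses LMM for both model types.

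A reader might also infer that the plan has decided against baseline adjustment for these outcomes. Silence does not show that. A condensed article may leave covariates to the analysis plans that the Dissemination Plan says will be preregistered. Randomization keeps an unadjusted comparison valid, and no power is claimed for these outcomes. All of that stands, so the absent covariate list is not itself an error.

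The simulation inputs are partly guesses. Sample Size Calculations equates 0.4 with 4 points, which implies an SD of 4/0.4 = 10 rather than 6.5. Using 6.5 as the posttreatment SD implies a change SD of √(4² + 6.5² − 2 × 0.5 × 4 × 6.5) = 5.7 at baseline SD 4, or 5.9 at SD 5. The efficiency gain is insensitive to the effect size: with a 4-point difference it was again about 5% at correlation 0.3 and 13-15% at 0.5. Absolute power is not insensitive in this way and should not be relied on.

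**Conclusion.** The concern holds in a limited form. The rationale given for omitting the group term cannot apply to response and remission, and the text leaves open whether the model is meant for them. A posttreatment difference fixed at zero is a possible result of one way of applying the text, not something the plan prescribes.

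The conflict over scoring visits holds on any reading: as defined on Y-BOCS I, both outcomes can be scored at posttreatment only, against four visits in Table 1.

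The gain from adjustment is for remission: roughly 5% in efficiency at correlation 0.3, 12-16% at 0.5 and about 25% at 0.6. It rests on assumed baseline mean, SD, correlation and sham change. For response the benefit is clarity about the treatment term, with almost no power gain.

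**What to change.** 1. State that the model without a group term applies only to outcomes measured at baseline: Y-BOCS II, CGI, EQ-5D-5L, BDI, BAI and YGTSS.
2. For response and remission, specify a logistic model with an explicit group effect at posttreatment, and at any later visit actually scored, adjusted for baseline Y-BOCS I and study center. Name the posttreatment group effect as the parameter of interest.
3. Reconcile Table 1 with the Y-BOCS I schedule: either restrict both outcomes to posttreatment or say how they are scored at FU1-FU3. Settle the remission cut-off at the same time (below 12, or 12 and below).
4. Report crude proportions by arm beside the adjusted odds ratios.

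The cost is a few sentences. The adjustment uses data already collected, and the change can be made before unblinding. The downside is that the odds ratio becomes conditional on baseline severity and lies slightly further from 1 than the crude one, which is why the crude proportions should accompany it.

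### Side effects are to be reported as absolute numbers under 2:1 allocation, so bare counts are not directly comparable between arms (minor)

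*Protocol article*

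**What the plan says.** Tolerability is a listed secondary clinical outcome in the Outcome Measures section: "Tolerability of the treatment and side effects, using an in-house questionnaire developed as part of our previous TIPICCO trial". Table 1 has side effects assessed weekly during treatment.

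The reporting format is in Secondary Study Parameters- Clinical: "Tolerability and side effects will be reported as absolute numbers and described qualitatively". The opening of Statistical Analyses adds only this: "Safety data (eg, side effects and serious adverse events) are collected and summarized in the study results".

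On arm sizes, the Randomization section states: "Participants are randomized in a 2:1 ratio to one of 2 treatment arms, with twice as many participants allocated to receive active stimulation". Sample Size Calculations gives the evaluable numbers, "the study requires 150 participants in the verum-rTMS arm and 75 in the sham-rTMS arm", and the enrolment target: "Assuming a 10% dropout rate, we will include (225/0.9=) 250 participants".

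No section gives a denominator, a percentage, a rate or a between-arm contrast for side effects. None says whether the numbers are of participants or of events.

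**The concern.** The article does not leave the format of the side-effect results open; it names one. That format suits a single-arm report or equal arms. Here one arm is twice the size of the other by design, so a count carries the allocation ratio as well as the risk. Followed literally, the sentence produces a table in which the two columns cannot be read against each other without further work.

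What is at stake is the clarity of the tolerability results. A side effect that is equally common in both arms would tend to look more common on active stimulation, and one that is more common on sham could look balanced.

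There is a second, conditional issue. If the numbers are events added up over weekly forms, they also depend on how long each participant was treated, and treatment length varies from 20 to 28 sessions.

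**Working it through.** **Inputs from the protocol article**
- Allocation 2:1 (Randomization).
- 150 active and 75 sham evaluable; 250 enrolled after allowing for 10% dropout (Sample Size Calculations).
- Standardised effect 0.4, two-sided alpha 0.05, power 0.8 (Sample Size Calculations).
- Four sessions per week, 20 to 28 sessions (Study Design, Intervention); side effects assessed weekly (Table 1).

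**Assumption.** The article gives no side-effect risk. The risks below are assumed and shown as a range.

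**Step 1: the plan's own arm sizes.** With two active participants per sham participant, the normal approximation gives sham n = (1.96 + 0.842)² × (1 + 1/2) / 0.4² = 73.6, rounded up to 74, so 74 + 148 = 222. The t-test version gives 74.2, rounded up to 75, so 75 + 150 = 225. Then 225 / 0.9 = 250. The stated figures reproduce. Splitting 250 in the ratio 2:1 gives 166.7 and 83.3, about 167 and 83.

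**Step 2: expected counts at a common risk r.** Expected affected participants are n_active × r and n_sham × r. Their ratio is n_active / n_sham = 2.0, whatever r is.

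| Assumed risk, both arms | 150 vs 75 evaluable | 166.7 vs 83.3 enrolled |
|---|---|---|
| 5% | 7.5 vs 3.8 | 8.3 vs 4.2 |
| 10% | 15.0 vs 7.5 | 16.7 vs 8.3 |
| 20% | 30.0 vs 15.0 | 33.3 vs 16.7 |
| 30% | 45.0 vs 22.5 | 50.0 vs 25.0 |

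**Step 3: how often the active count would be the larger.** The 2.0 is an expected value, and observed counts vary around it. With two independent binomials (167 and 83) and the same risk in each, the probability that more participants are affected on active is 0.70 at 2% risk, 0.86 at 5%, 0.95 at 10% and 0.995 at 20%.

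**Step 4: the reverse case.** Suppose 20 participants are affected in each arm (an illustrative count). With 167 and 83, that is 20/167 = 12.0% against 20/83 = 24.1%, a difference of -12.1 percentage points (Newcombe 95% CI -23.1 to -2.3). With 150 and 75 it is 13.3% against 26.7%. Equal counts therefore correspond to twice the risk on sham.

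**Step 5: only if events are counted.** At four sessions per week, 20 sessions take 5 weeks and 28 take 7. At a constant weekly event rate, a participant treated for 28 sessions contributes 7/5 = 1.4 times the events of one treated for 20. Dividing by arm size does not remove this. It distorts the comparison between arms only if treatment length differs between arms.

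**The case against.** The strongest reply is that the sentence follows a list of outcomes to be modelled or tested. Read naturally, it says that side effects will be tabulated and described, not tested. It does not prescribe a comparison of raw counts between arms and does not forbid percentages. Arm sizes will be known: the allocation is published, and the legend to Figure 2 promises final CONSORT figures. A reader shown 50 and 25 affected participants out of 167 and 83 recovers 30% in each arm. Details such as the safety population are often left to a full protocol or analysis plan, and the Dissemination Plan says analysis plans will be preregistered.

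Most of this stands, and it is why the point is minor. It does not remove the point. The article names a format, nothing else in it supplies a denominator, and a reader should not have to rebuild a tolerability table. If the numbers are events, the percentage of participants affected cannot be rebuilt from them at all.

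Three stronger readings do not hold:
- **That the trial will present active rTMS as twice as harmful.** This requires a reader who ignores the stated allocation.
- **That variable treatment length biases the comparison.** The article does not say that events are counted. The Intervention section describes the continuation decision as independent of allocation. Because extension depends on continued improvement or motivation, length could differ between arms if active stimulation works, but the article gives neither the direction nor the size of any difference.
- **That the side-effect tables bear on reimbursement.** The Dissemination Plan points chiefly to the cost-effectiveness analysis, and Outcome Measures names QALYs as the key measure for such decisions.

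**Conclusion.** The concern holds as a minor one. Absolute numbers alone do not suit a 2:1 design: at a common risk the expected ratio of affected participants is 2.0, and equal counts mean twice the risk on sham. The ratio rests only on the article's own allocation. The particular counts rest on assumed risks, and the enrolled arm sizes on a 2:1 split of 250.

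The effect is confined to how one descriptive secondary outcome is presented. The primary analysis, the power and the cost-effectiveness analysis are unaffected. The exposure point is conditional: it applies only if recurrent events are counted and treatment length differs by arm.

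**What to change.** Replace the sentence in Secondary Study Parameters- Clinical with one that reports, per arm, the number and percentage of participants with each side effect, among those who received at least one session. Add the between-arm risk difference with a 95% CI, stated to be descriptive, untested and not adjusted for multiplicity. State whether participants or events are counted. If recurrent events from the weekly forms are counted, also give the rate per week or per session observed.

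The cost is one or two sentences in the article's successor text or the preregistered analysis plan. The data are already being collected, and the change can be settled before unblinding. The small downside is a set of unadjusted intervals, some of which may exclude zero by chance; labelling them descriptive deals with that.
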